### Exclusion Criteria

Patients who meet the following criteria will be excluded from participation: (1) preexisting psychiatric disorders diagnosed by a psychiatrist before contracting COVID-19; (2) inability to respond to the questionnaire; (3) concurrent neurological disorders, such as stroke with sequelae, Alzheimer disease, and Parkinson disease; (4) individuals subjected to invasive mechanical ventilation during their COVID-19 infection; or (5) those experiencing persistent fatigue symptoms within the 6 months before SARS-CoV 2 infection.

The study design and inclusion criteria will be reviewed regularly to ensure they align with current best practices and the latest understanding of COVID-19. A patient enrollment flowchart is presented in Figure 1.

**Figure 1 figure1:**
[figure not shown]
Study flowchart. CFQ-11: Chalder Fatigue Scale; HADS: Hospital Anxiety and Depression Scale; PTSS-14: 14-item Posttraumatic Stress Scale.

### Data Collection

Data collection will take place during appointments at the long COVID follow-up clinics in all participating hospitals. Qualified clinical study staff will gather the data using a clinical research form (CRF) (Multimedia Appendix 1). These individuals comprise health care professionals, such as nurses, clinical research coordinators, and health care experts who have received appropriate training and have the necessary expertise to conduct data collection and assessments in a clinical research setting. Their training ensures adherence to research protocols and ethical guidelines, guaranteeing accurate and consistent data gathering during clinical appointments. Two months after hospital discharge, we will mail all patients a letter offering a follow-up consultation in the outpatient clinic. Patients who agree to attend will be offered 2 appointments, consisting of an anamnesis and a physical examination, and given several self-administered tests in the waiting room. We will allocate 15 minutes for the questionnaire completion in the waiting room. In the first visit (T1, 3 months), the following data will be additionally collected: demographic characteristics like age, sex, and BMI (kg/m^2^); each participant’s medical history, such as the date of the first positive COVID-19 test (PCR or antigen) and smoking, alcohol, and drug consumption status; comorbidities and usual medication intake; and screening of symptoms and severity of the acute disease. Data collection in the second visit (T2, 6 months) will include post–COVID-19 symptoms, the Chalder Fatigue Scale [26] (CFQ-11), the Hospital Anxiety and Depression Scale (HADS) [27], the 14-item Posttraumatic Stress Scale (PTSS-14) adapted to COVID-19, and the EQ-5D [28] questionnaire.

### Ethical Considerations

This study involves human participants and has adhered to all applicable ethical standards and procedures. The Algarve University Hospital Centre Ethical Committee approved this study (141/21; Multimedia Appendix 2). The patients’ race will not be included in the study because the ethics committee did not approve this differentiation. A paper-based consent form was previously approved by the ethics committee. This consent form has 2 components: information for the participant (regarding the project) and declaration of informed consent (to date and sign, in case of acceptance). The informed consent procedure, mailed to potential participants, will provide them with detailed information about the study’s objectives, risks and benefits of participation, and data management practices (Multimedia Appendix 3). The study will follow ethical guidelines and regulations related to informed consent, and participants will have the opportunity to ask questions and provide voluntary consent before enrolling. Participants will be given a month for reflection before written informed consent. As for data management, the study will implement a secure and confidential system that uses data encryption and secure storage procedures to protect participant confidentiality and comply with data protection laws and regulations. Only authorized individuals who have a legitimate need to access the data will be permitted to do so, and any data sharing will be done in compliance with the relevant ethical and legal requirements. As applicable, all procedures from this investigation followed the Declaration of Helsinki. All researchers will comply with the Data Protection Acts of their respective academic institutions.

### Primary Outcome

#### Fatigue

A validated fatigue assessment tool will be used at the follow-up visit to capture a broader range of participants. This will provide a more comprehensive understanding of the relationship between fatigue and mental symptoms in individuals with long COVID. Fatigue will be measured using the CFQ-11 [26]. This is an 11-item self-report measure of physical and mental fatigue. Participants rate their fatigue experienced over the past month compared to their usual energy levels using a 4-point Likert scale ranging from 0 (“less than usual”) to 3 (“much more than usual”) [29]. Scores range from 0 to 33. A bimodal version can also be calculated, where scores range from 0 to 11, with a cutoff score of 4 or more indicating a case of fatigue [29]. Reliability coefficients for the CFQ-11 have been shown to range between 0.8 and 0.9 [29-31] in both patients with chronic fatigue and the general population. This study will use only the Likert scale to reduce the risk of ceiling effect bias.

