**Methods:**

Using a consecutive nonrandom sampling technique, we will conduct a prospective cohort multicenter observational study in 5 Portuguese hospitals. Symptomatic adult patients with previous COVID-19 attending follow-up consultations will be enrolled. We will include patients who had mild, moderate, and severe acute disease. We will assess clinical outcomes related to COVID-19, including the type of respiratory support such as high-flow nasal cannula, noninvasive ventilation, and invasive mechanical ventilation. The exclusion criteria will include previous severe psychiatric disorders confirmed by a psychiatrist; refusal or inability to respond to the questionnaire; concomitant neurological disorder; persistent fatigue symptoms during the 6 months before infection; and the need for invasive mechanical ventilation during COVID-19 infection due to a high prevalence of postintensive care syndrome. Our primary outcome is the prevalence of fatigue in patients with post–COVID-19 depression and/or anxiety, as measured by the Chalder Fatigue Scale (CFQ-11) and the Hospital Anxiety and Depression Scale (HADS). The secondary outcomes will include an assessment of health-related quality of life via the EQ-5D questionnaire and an exploration of the prevalence of symptoms of posttraumatic stress disorder (PTSD) using the 14-item Posttraumatic Stress Scale (PTSS-14). We will also examine the association between mental health symptoms and the severity of acute COVID-19. The post–COVID-19 data will be collected at least 6 months after the positive test and no longer than 9 months during the clinical appointment.

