Research questions of the study.Research Question 1 (primary outcome):Do patients with long COVID who experience depression and/or anxiety symptoms have a higher prevalence of fatigue?Research questions 2 to 4 (secondary outcomes):Is there a correlation between the type of fatigue and depression and/or anxiety symptoms among patients post COVID-19?Is there a correlation between fatigue and the presence of PTSD symptoms in patients post COVID-19?Do patients with fatigue associated with mental health disorders have a lower health-related quality of life (HRQoL) after COVID-19?

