The 5 phases of the statistical analyses carried out in this study.Phase 1: Characterization of the patient sample1.1. Sociodemographic analysis of the variables collected at T1 and the variables from the surveyed instruments at T2. This involves descriptive analysis, both univariate and bivariate, which will be differentiated by:1.1.1. Quantitative variables: mean and SD, coefficient of variation, and median and IQR1.1.2. Qualitative variables (nominal and ordinal categorical): analysis of distributions through absolute and relative frequencies, including absolute and relative accumulated frequencies1.1.3. Quantitative variables will be reported alongside appropriate tests for normal distribution to ensure the accuracy and validity of our statistical analyses.1.2. Bivariate and descriptive analysis using 2D tables will be calculated for all qualitative variables belonging to T1 with all instrument scores collected at T2: Chalder Fatigue Scale (CFQ-11), Hospital Anxiety and Depression Scale (HADS), 14-item Posttraumatic Stress Scale (PTSS-14) adapted to COVID -19, and EQ- 5D plus recorded COVID-19 symptoms. The previous points will be reiterated in this bivariate context, utilizing the computational aid of split->file categorical variables in situations where one variable is metric and the other is categorical.1.3. Internal consistency and reliability analysis of the T2 instruments: calculation of the Cronbach alpha (general and partial) for all ordinal items and item subgroups differentiated by the subscales defined by the respective authorsPhase 2: Determination of fatigue incidence caused by long COVID and its relationship with T1 and T2 variables2.1. Procedures for determining fatigue cutoff points in this cohort of patients:2.1.1. Bivariate analysis using optimal binning procedures for categorical variables (age class, sex, and BMI) with the total fatigue score, as well as partial scores of physical and psychological fatigue2.1.2. Multivariate analysis by constructing models in the format of decision trees via the CHAID (chi-square automatic interaction detection) algorithm [41], with total and partial fatigue scores as dependent variables2.2. Inferential analysis based on variables resulting from 2.1.1 and/or 2.1.2, considering the complexity of variables in T1 and T2:2.2.1. (1) Chi-Square tests to capture the association of categorical variables; (2) Shapiro-Wilk tests to verify the distribution of quantitative variables; (3) tests for comparing 2 or more population means: parametric analysis of variance (ANOVA) test and nonparametric (Kruskal-Wallis) test; and (4) correlation tests (Spearman or Pearson) to verify the degree of association between T2 instrument scalesPhase 3: Determination of patient groups based on fatigue differentiation3.1. Conducting classification analysis using clustering techniques, specifically the 2-step cluster analysis, to explore variables with greater power in differentiating groups of patientsPhase 4: Exploration of the best combination of T1 and T2 variables capable of discriminating patient fatigue levels through a discriminant multivariate analysisPhase 5: Investigation of the association between phase 3 groups and all T2 instrument scales using chi-square association tests

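### The primary outcome is a fatigue prevalence, but the plan fixes no fatigue case definition and derives its cutoffs from the same patients it then analyses

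*Protocol article*

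**What the plan says.** All references are to the Protocol article.

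- **Outcome.** The Abstract (Methods) states: "Our primary outcome is the prevalence of fatigue in patients with post–COVID-19 depression and/or anxiety". Research Question 1 in Textbox 1 makes it a comparison: "Do patients with long COVID who experience depression and/or anxiety symptoms have a higher prevalence of fatigue".
- **Case definition.** The Fatigue section under Primary Outcome describes two scorings of the CFQ-11: a Likert total from 0 to 33 and a bimodal total from 0 to 11. Only the bimodal one comes with a case rule, "with a cutoff score of 4 or more indicating a case of fatigue". The section ends: "This study will use only the Likert scale to reduce the risk of ceiling effect bias". No cutoff on the 0-33 scale appears anywhere in the article.
- **Where the cutoff comes from.** Textbox 2, item 2.1, is titled "Procedures for determining fatigue cutoff points in this cohort of patients". Item 2.1.1 reads "Bivariate analysis using optimal binning procedures for categorical variables (age class, sex, and BMI) with the total fatigue score", and extends this to the physical and psychological subscores. Item 2.1.2 reads "Multivariate analysis by constructing models in the format of decision trees via the CHAID" algorithm, with fatigue scores as dependent variables and no predictors named.
- **What is then tested.** Item 2.2 is "Inferential analysis based on variables resulting from 2.1.1 and/or 2.1.2". It lists chi-square tests, ANOVA or Kruskal-Wallis, and Spearman or Pearson correlations between the T2 scales. Textbox 2 mentions no hold-out sample, validation or correction for the cutoff search.

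**The concern.** A prevalence cannot be computed without a case rule. Here the one cited rule belongs to a scoring the study says it will not use, and the replacement is to be found in the data. Binning three fatigue scores against three guide variables can give several different cutoffs. The and/or in item 2.2 leaves open which procedure supplies the one that counts. A cutoff chosen because it separates ages, sexes or BMI classes is also not, for that reason, a cutoff that identifies fatigued patients.

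Two things are at stake. The first is the meaning of the primary result: it could be compared neither with the planning figure of about 50% in Power and Sample Size nor with studies that use a published cutoff. The second is the validity of the later tests. A cutoff picked to separate groups and then tested on those groups in the same patients gives P values that are too small.

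**Working it through.** **Step 1. Is a case rule fixed anywhere?**

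| Needed for a prevalence | What the article gives |
|---|---|
| A score | CFQ-11 Likert, 0-33, used exclusively |
| A cutoff on that score | None |
| A cutoff on another score | Bimodal, 4 or more of 11, but that scoring is not used |
| A substitute | Cutoffs to be found in this cohort (Textbox 2, 2.1) |

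The article does more than leave a detail open. It rejects one rule and commits to a data-derived route.

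**Step 2. How much does the cutoff matter?**
The article gives no score distribution, so one is assumed: 11 correlated items scored 0-3, with total mean 18.4 and SD 7.7. The share of patients at or above each Likert cutoff is then:

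- 12 or more: 80%
- 16 or more: 62%
- 18 or more: 53%
- 22 or more: 35%
- bimodal 4 or more, same answers: 67%

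A shift of 10 points on the 33-point scale changes prevalence by 80 − 35 = 45 percentage points. The exact figures depend on the assumed distribution; the dependence on the cutoff does not.

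**Step 3. What happens to the tests?**
The setting was 200 patients split 100:100, as in Power and Sample Size, with no true association. There were 5,000 simulated studies, each with a 2×2 chi-square test at 0.05. The cutoff maximised chi-square against a binary guide variable, with a minimum share of patients on each side. That criterion is an assumption, because Textbox 2 names none.

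| How the cutoff is set | Variable tested | False positives |
|---|---|---|
| Fixed, bimodal 4 or more | HADS group | 5.0% |
| Optimised on a guide variable, at least 10% each side | the same guide variable | 31% |
| As above, at least 25% each side | the same guide variable | 19% |
| Optimised on HADS group, at least 10% each side | HADS group | 32% |
| As above, at least 25% each side | HADS group | 20% |
| Optimised on a guide variable independent of HADS | HADS group | 5.1% |
| Guide variable and HADS at latent correlation 0.3 | HADS group | 5.6% |
| Guide variable and HADS at latent correlation 0.6 | HADS group | 9.6% |

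**Step 4. Does the algorithm matter?**
Yes. With an entropy binning rule that accepts a cut only when the gain exceeds a description-length penalty, a cut was accepted and then significant in about 0.2-0.3% of null data sets with a two-level guide variable. The rate against the guide variable thus runs from under 1% to about 30%, depending on a choice the article does not state.

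**Step 5. What does CHAID do?**
Item 2.1.2 makes the fatigue score the dependent variable. A tree of that kind splits the predictors and does not itself cut the fatigue score. How it would yield a fatigue cutoff is not explained, and the simulation does not represent it.

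**The case against.** The strongest reply is that the primary comparison is not shown to be biased. A reader might infer from Textbox 2 that every P value in Phase 2 is too small. The article does not support that. The only binning variables it names are age class, sex and BMI. HADS is not among them, and a cutoff set on an unrelated variable leaves the fatigue-versus-HADS test at about 5%. CHAID predictors are unnamed. Phase 2 covers T1 and T2 variables and HADS is collected at T2, so its entry cannot be excluded, but it cannot be assumed either. Correlations and mean comparisons that use the uncut Likert score involve no derived cutoff and are unaffected. This part of the reply stands.

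A reader might also take the spread of prevalence at noise-optimised cutoffs, 12% to 89% (5th to 95th percentile), as a measure of this study's instability. It largely restates the search window. With at least 25% of patients required on each side, the spread becomes about 27% to 74%. It should not be quoted as an estimate.

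Two further replies have some force. The authors give a reason for Likert scoring, the ceiling effect, and a prespecified Likert cutoff or a validated derived one would also repair the plan. And an article may leave detail to a fuller document. But the ceiling argument concerns measuring severity and gives no reason to go without a case rule. The data-derived route is also stated outright, so it is not merely a missing detail.

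**Conclusion.** The point holds on the text for the case definition, and only conditionally for the P values.

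- **Firm:** the primary prevalence has no prespecified case rule, and its replacement depends on the sample and on an open choice of procedures. It cannot be set against the 50% planning figure or against other studies. This needs no simulation.
- **Conditional:** tests of derived fatigue categories against the variables that set the cutoff have inflated error. The rate is about 20-30% under an unpenalised chi-square search and could be far lower under a penalised algorithm. These rates are illustrative.
- **Not shown:** inflation of the primary fatigue-versus-HADS test. It stays near 5% unless HADS helps set the cutoff or is strongly correlated with the guide variables, reaching about 10% at an assumed latent correlation of 0.6.

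The size of the prevalence shift rests on the assumed score distribution in Step 2.

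**What to change.** 1. Prespecify one fatigue case definition for the primary outcome. The simplest is the bimodal CFQ-11 score of 4 or more, which the Fatigue section itself says can be calculated; it is a recode of the same 11 answers. A Likert cutoff fixed in advance from an external source would also serve.
2. Keep the 0-33 Likert total and the physical and psychological subscores for severity and correlation analyses, and limit the Likert-only sentence to those.
3. Label the Phase 2.1 cutoffs exploratory. Do not use them to define the primary outcome or in confirmatory Phase 2.2 tests, unless they are validated in separate data or the tests are corrected for the cutoff search. There is no need to bar P values from Phase 2.1 altogether.
4. If the derived cutoffs are kept for exploration, name the binning criterion, the CHAID predictors and how the tree is meant to yield a fatigue cutoff.

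The cost is analysis-plan wording and a recode, with no new data. Case status discards some information, which the retained Likert analyses cover.

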### Secondary Outcomes

#### Depression and Anxiety

Symptoms of depression and anxiety will be assessed using the HADS [27], a practical, validated tool for assessing symptom severity in anxiety and somatic disorders in psychiatric and primary care settings and the general population [32]. This measure comprises 14 items, 7 measuring symptoms of anxiety and 7 measuring symptoms of depression. The scores are categorized into different ranges: 0 to 7 as “normal,” 8 to 10 as “mild,” 11 to 14 as “moderate,” and 15 to 21 as “severe.” The HADS questionnaire has been validated in many different languages and settings [32-34].

#### HRQoL Assessment

HRQoL will be assessed using the original EQ-5D questionnaire, which comprises 2 parts. The first part is the EQ-5D-3L questionnaire [28], a health state classification scheme of 5 items (mobility, self-care, usual activities, pain/discomfort, and anxiety/depression), each having 3 alternatives (1=no problems, 2=moderate problems, and 3=severe problems). The combination of answers for the 5 items represents the health state (given as an index), ranging from 0 (worst possible health state) to 1 (best possible health state). The second part comprises the EuroQol Visual Analog Scale (EQ-VAS), which represents health states in a range from 0 (the worst possible health state) to 100 (the best possible health state). The EQ-5D can distinguish between the health conditions of patients with diverse injuries [35,36] and has been validated in several populations [37].

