Fatigue, a primary persistent symptom of long COVID, has been reported in 10% to 70% of patients [16-19]. It is defined as “a decrease in physical or mental performance that results from changes in central, psychological, or peripheral factors due to the COVID-19 disease” [20]. Thus, post–COVID-19 fatigue depends on conditional and psychophysiological factors comprising the individual’s task, environment, physical, and mental capacity, as well as the disease’s central, psychological, and peripheral aspects [20].

While fatigue is not traditionally considered a neuropsychiatric disorder, it can be a symptom of many mental health conditions, such as depression, anxiety, and posttraumatic stress disorder (PTSD) [21,22]. Therefore, it is often included in discussions of mental health symptoms in post–COVID-19 syndrome [23]. The term “neuropsychiatric” often refers to a wide range of disorders affecting the brain and mental health. In contrast, “neuropsychological” refers to studying the relationship between brain function and behavior [24]. The primary focus of this study is on psychiatric symptoms, particularly depression and anxiety. However, we will also investigate PTSD, which is a neuropsychiatric disorder involving both neurological and psychiatric aspects. In addition, the health-related quality of life (HRQoL) assessment includes a section that evaluates aspects related to anxiety and depression. While not designed for diagnosing psychiatric disorders, this assessment can help gauge how these symptoms affect a person’s overall quality of life, making it more of a general health assessment.

The current literature on long COVID and its mental sequelae has relied on self-reported symptoms through questionnaires administered either in-person or through telephone interviews to comply with public health guidelines. However, the correlation between these self-reported symptoms needs to be clarified. There is an obvious need to accurately characterize the mental sequelae of COVID-19 and the risk factors associated with these outcomes.

This study aims to quantify the degree of physical and psychological fatigue in patients post COVID-19 and assess the correlation of fatigue with other mental sequelae—particularly depression, anxiety, and PTSD. Furthermore, we aim to explore its impact on HRQoL.

Our research questions for this study are outlined in Textbox 1.

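### Research Question 4 tests whether mood-related fatigue goes with lower HRQoL using an EQ-5D index that contains an anxiety/depression item, so part of any index difference is built in

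*Protocol article*

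**What the plan says.** Textbox 1 in the Introduction poses Research Question 4 (RQ4): "Do patients with fatigue associated with mental health disorders have a lower health-related quality of life (HRQoL) after COVID-19". The Introduction says which disorders are chiefly meant: "The primary focus of this study is on psychiatric symptoms, particularly depression and anxiety"; PTSD is also examined. The Depression and Anxiety section names the instrument: "Symptoms of depression and anxiety will be assessed using the HADS".

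The HRQoL Assessment section describes two parts of the outcome. The first is the EQ-5D-3L, whose items are "mobility, self-care, usual activities, pain/discomfort, and anxiety/depression". Each has three levels, and all five feed one index from 0 to 1. The second is the EQ-VAS, a single rating from 0 to 100.

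The Introduction is aware of the shared content. It says that the HRQoL assessment "includes a section that evaluates aspects related to anxiety and depression" and presents this as a help in gauging how such symptoms affect quality of life. Textbox 2 (Statistical Analyses) does not return to the matter: Phase 2 correlates the T2 scales and Phase 5 relates the Phase 3 groups to all T2 scales, with no separate handling of the shared item. The Limitations section does not mention it.

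**The concern.** Anxiety/depression helps to define who is compared in RQ4 and is also one of the five items of the index on which they are compared. Patients with raised HADS scores will usually report more problems on the EQ-5D mood item because the two self-reports ask about the same thing. The index then falls even if mobility, self-care, usual activities and pain are the same in both groups.

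What is at stake is interpretation. A yes to RQ4 would be read as mood-related fatigue going with a worse life overall. The Expected Findings section already moves in that direction, suggesting that addressing anxiety symptoms may improve quality of life. An index gap that comes from the mood item alone would not support that step, and the index by itself cannot show where the gap comes from.

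**Working it through.** The document gives no figure for this overlap, no value set for the index and no item frequencies. There is no stated figure to reproduce, and everything below is an illustration under assumptions.

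**Step 1: the overlap.** The construct that marks out the RQ4 patients is mainly depression/anxiety (Introduction; Depression and Anxiety). The outcome items include anxiety/depression (HRQoL Assessment). One item in five is shared with the index, none with the EQ-VAS.

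**Step 2: size of the built-in difference.** Assume an equal-weight index, 1 − (sum of five item levels, each scored 0, 1 or 2)/10. Give the four non-mood items the same distribution in both groups (about 42% with any problem, 5% severe) and a correlation of 0.3 to 0.5 on the underlying scale. Only the mood item differs:

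| Contrast | Mood item, with symptoms (none/moderate/severe) | Without symptoms | Mean levels | Index difference | SD | d |
|---|---|---|---|---|---|---|
| Strong | 10/65/25% | 80/19/1% | 1.15 vs 0.21 | 0.093 | 0.162–0.182 | 0.51–0.57 |
| Moderate | 25/60/15% | 65/33/2% | 0.90 vs 0.37 | 0.053–0.054 | 0.165–0.184 | 0.29–0.33 |
| Weak | 40/52/8% | 60/37/3% | 0.68 vs 0.43 | 0.025 | 0.165–0.185 | 0.13–0.15 |

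The index difference is the gap in mean levels divided by 10: for the strong case (1.15 − 0.21)/10 = 0.094, against 0.093 by simulation. Then d = difference/SD, for example 0.093/0.182 = 0.51 and 0.093/0.162 = 0.57. With the mood item removed, d is about 0, as it must be by construction.

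**Step 3: sensitivity to the assumptions.** A second set uses non-mood items at 60/35/5%, inter-item correlation 0.2–0.4, and mood items of 10/70/20% vs 80/20/0% (strong), 30/60/10% vs 70/30/0% (moderate) and 40/50/10% vs 60/35/5% (weak). It gives d of 0.48–0.58, 0.26–0.31 and 0.12–0.15. If the mood item carries half the weight of the others, d falls to 0.26–0.31, 0.14–0.17 and 0.07–0.08.

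**Step 4: group size for RQ4.** Power and Sample Size plans 100 patients with and 100 without adverse mental health symptoms. If 250 are enrolled and 25% are lost, 250 × 0.75 / 2 ≈ 94 per group remain. RQ4 concerns fatigued patients. With the document's expected fatigue prevalence of around 50%, assumed equal in both groups, that leaves 94 × 0.5 = 47 to 100 × 0.5 = 50 per group.

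**Step 5: chance that the built-in difference alone reaches p<.05.** Two-sided two-sample t test, 2n − 2 degrees of freedom, noncentrality d × √(n/2), with the d values of the second set:

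- Strong: 0.48 × √23.5 = 2.33 gives 63%; 0.58 × √25 = 2.90 gives 82%.
- Moderate: 0.26 × √23.5 = 1.26 gives 24%; 0.31 × √25 = 1.55 gives 34%.
- Weak: 0.12 × √23.5 = 0.58 gives 9%; 0.15 × √25 = 0.75 gives 12%.

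The d values of Step 2 give similar figures: 69–81%, 29–37% and 10–12%.

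**The case against.** Four points deserve weight.

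- **No such test is prescribed.** The article does not say that the index will be compared between HADS-defined groups. RQ4 names no comparator, and Phase 5 uses clusters based on fatigue and chi-square tests. This stands: the t test above is only a way of sizing the effect. But the question, the five-item index and the analysis phases are fixed in the article, and any comparison of groups that differ in anxiety/depression meets the shared item.
- **Mood belongs to HRQoL.** A patient who is worse only on the mood item does have lower HRQoL as this instrument defines it. This also stands, and is a reason to keep the index. It does not justify reading an index gap as evidence of an effect beyond mood.
- **The material for a remedy is collected.** The EQ-VAS lacks the item, and Phase 1 can be read as tabulating the item responses. But no comparison by dimension between the RQ4 groups is described. The EQ-VAS is not a clean substitute either, since a global self-rating can also reflect mood.
- **The figures rest on assumptions.** They do: frequencies, correlations and weights are all assumed, and exactly no difference on four items is a limiting case.

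A reader might go further and infer that RQ4 is circular and cannot be answered. The document does not support that: HADS is a separate 14-item instrument, four of the five EQ-5D items do not ask about mood, the EQ-VAS does not contain the item, and the disorders may include PTSD. A reader might also apply the full 94–100 per group, where the second set gives p<.05 in about 89–97%, 44–57% and 14–18% of studies. Those figures do not fit a contrast within fatigued patients.

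**Conclusion.** The concern holds in a limited form. Part of any difference in the EQ-5D-3L index between groups that differ in anxiety/depression is built in, and the article notes the item without addressing the consequence for RQ4. The size cannot be determined from the document. Under the assumptions shown it runs from d of about 0.13 to 0.57, roughly halved at half weight. With 47–50 fatigued patients per group, the chance of a significant index difference from this source alone runs from about 9–12% to 63–82%. That range shows that the effect could matter, not that it will.

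This is a matter of what a secondary question can conclude. It does not touch the primary outcome. The unnamed comparator in RQ4 is a separate point.

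**What to change.** In the analysis text for RQ4:

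- Keep the five-item index.
- Beside it, compare the EQ-VAS and each of the five EQ-5D dimensions between the same groups, with the anxiety/depression item shown on its own.
- Attribute lower HRQoL beyond mood only if the non-mood dimensions also differ, with the EQ-VAS as support.
- Add the shared item to the Limitations.

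Naming the EQ-VAS as the lead measure is optional.

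The cost is a few table rows and a sentence or two; no new data are needed. The downside is that the headline HRQoL difference may turn out smaller.
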